### Nuclear medicine imaging techniques

An ECG-gated MPS and a ^18^F-FDG PET scan are performed at baseline (approximately two weeks before CABG) and more than three weeks after CABG. Stress and rest myocardial perfusion scintigraphy (with single-photon emission computed tomography (SPECT)) is performed with ^99 m^Tc labeled Tetrofosmin. Symptom limited exercise is the preferred stress modality. Pharmacological vasodilatory stress with adenosine will be applied if there is an insufficient increase of heart rate (<85% age predicted maximal heart-rate) during physical exercise, in the presence of a left bundle branch block, or if the anti-anginal medication had not been adequately discontinued. Dobutamine stress testing is performed in patients with a contra-indication for adenosine. The type of stress test applied for MPS before surgery is maintained at the MPS post-surgery. ECG-gated image acquisition is performed for the assessment of parameters of left ventricular function (end-systolic and end-diastolic volumes and ejection fraction). Two experienced nuclear medicine physicians analyze the images in a total of 17 myocardial segments. Segments are scored with a 5-point scoring system (0 = normal; 1 = equivocal; 2 = moderate reduction; 3 = severe reduction; 4 = absent activity). Summed stress score (SSS) and summed rest score (SRS) are obtained by adding the scores of all segments of respectively stress and rest images. The summed difference score (SDS) is calculated by subtracting the SRS from the SSS. Reversible myocardial perfusion defects, indicative for inducible myocardial ischemia, are defined as SDS ≥3. Fixed defects, indicative for scarring are defined as a SRS-score of ≥3. The presence of either reversible or fixed defects is defined as the presence of any perfusion defect.

^18^F-FDG is a glucose analogue that after cellular uptake via the GLUT-4 transporter and phosphorylation by hexokinase is not further metabolized. Therefore the imaged concentration of ^18^F-FDG in the heart reflects its glucose metabolism. Patients are imaged after suppression of the free fatty acid metabolism by oral administration of acipimox. The glucose metabolism in the myocardium is analyzed by standardized uptake values, both regional as for the total myocardium.

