### Outcome measures

The main study outcomes are amino acid profile and cardiomyocytes structure at the time of cardiac surgery. Amino acid profile will be studied in blood plasma and cardiac tissue and includes determining the concentrations of all amino acids, ADMA and symmetric dimethylarginine (SDMA, ADMA's isomer that lacks direct NOS inhibitory activity). In addition, the arginine/ADMA ratio (an indicator of potential NO production) will be calculated. In cardiac tissue, also the activity of dimethylarginine dimethylaminohydrolase (DDAH, an enzyme which degrades ADMA) and arginase (an enzyme which metabolizes arginine) are measured. Cardiomyocytes structure will be assessed by histological analysis, immuno-histochemistry, and by electron microscopy.

The secondary study outcomes are cardiac perfusion, left ventricular function and cardiac glucose metabolism. ECG-gated MPS will be used for the measurement of cardiac perfusion and left ventricular function. Cardiac glucose metabolism will be measured with ^18^F-FDG PET.

BIS measured FFM will be used as parameter of nutritional status. A high FFM is related to better nutritional status and improved post-surgical outcome [9]. Other outcome parameters are cardiac muscle damage and signs of failure as measured by blood plasma biomarkers (Troponin T, CK-MB, and NT-proBNP). Blood plasma will be stored for future study of metabolic switch biomarkers. Baseline characteristics (including European System for Cardiac Operation Risk Evaluation score (EuroSCORE) [10], and unintended weight loss) will be recorded, as well as clinical parameters (intensive care unit (ICU) stay, length of hospital stay, time of mechanical ventilation, organ failure, infections, bleeding, and postoperative mortality). Finally, the concentration of ADMA will be measured in a sample of the aortic wall to investigate the relation between tissue ADMA concentrations in the aorta, and both intracellular concentrations from peripheral blood mononuclear cells (PBMC) and plasma levels.

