### Statistical analysis

The results of the enteral and parenteral group will be compared with results of the control group. Differences between the (par)enteral and control group will be analyzed with Chi-square tests for categorical variables, with unpaired t-tests for continuous variables, and with the Mann-Whitney U test for non-normally distributed data. Correlations will be analyzed with Pearson's correlation or with the Spearman rank correlation coefficient. Multiple linear and multiple logistic regression models will be used to determine if differences between groups can be explained by the effect of (par)enteral nutrition, by confounders or by both. A p-value of ≤ 0.05 will be considered statistically significant.

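### The only perfusion results the protocol defines are yes/no defects; the full-scale scores behind them should be named as the perfusion endpoint and compared with adjustment for baseline

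*Protocol article*

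**What the plan says.** Outcome measures lists perfusion only in general terms: "The secondary study outcomes are cardiac perfusion, left ventricular function and cardiac glucose metabolism". The detail is in Nuclear medicine imaging techniques, in three steps.

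- **Grading.** Each of 17 segments gets a grade from 0 (normal) to 4 (absent activity): "Segments are scored with a 5-point scoring system".
- **Summing.** One total is formed for stress and one for rest: "Summed stress score (SSS) and summed rest score (SRS) are obtained by adding the scores of all segments". A third score is the gap between these two totals: "The summed difference score (SDS) is calculated by subtracting the SRS from the SSS".
- **Cutting.** The first label concerns ischaemia: "Reversible myocardial perfusion defects, indicative for inducible myocardial ischemia, are defined as SDS ≥3". A second label applies the same threshold to the rest total: "Fixed defects, indicative for scarring are defined as a SRS-score of ≥3". A third label is met when at least one of those two is met, and is called any perfusion defect.

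Scans are made about two weeks before and more than three weeks after CABG. Statistical analysis names no perfusion variable. Its general rule is that group differences "will be analyzed with Chi-square tests for categorical variables"; continuous data go to t-tests and non-normal data to Mann-Whitney tests. Regression models are foreseen to separate the effect of nutrition from confounding. Each arm has 16 patients.

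**The concern.** The same imaging section gives graded quantities for the two neighbouring outcomes: ventricular volumes and ejection fraction for left ventricular function, and standardized uptake values for glucose metabolism. Perfusion is the exception, because its description ends in three yes/no labels. A reader who carries out the plan from this text would naturally compare defect rates by chi-square.

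Aim 2 asks about perfusion before and after CABG. All arms are revascularised, so a nutrition effect would be an increment on top of surgery and could well be graded. If the labels carry the comparison, a patient whose SDS falls from 12 to 4 has not changed, while one who goes from 3 to 2 has lost the defect. With 16 per arm, the trial could report no perfusion effect from scores that would show one.

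**Working it through.** **Inputs from the protocol.** There are 17 segments scored 0 to 4, so SSS and SRS each run from 0 to 17 × 4 = 68. The cut is at 3, with 16 patients per arm and significance at p ≤ 0.05 (two-sided assumed). The article gives no power, effect size, score distribution or defect rate, so there is no figure of its own to reproduce. Everything below rests on assumed distributions.

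**1. Information kept by one cut.** For a normal score cut at c, with a fraction p of controls above it, the efficiency relative to the full scale for a small shift is φ(c)² / [p(1 − p)].

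- p = 50%: 0.399² / 0.25 = 0.64
- p = 70%: 0.348² / 0.21 = 0.58
- p = 80%: 0.280² / 0.16 = 0.49

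The loss is therefore 36% to 51%. In patient terms, 16 per arm works like 16 × 0.64 ≈ 10 down to 16 × 0.49 ≈ 8.

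**2. Power for a normal score with a 1 SD shift.** The t-test (noncentral t, 30 degrees of freedom, noncentrality 1.0 × √(16/2) = 2.83) has 78.1% power. The power of the uncorrected chi-square test comes from enumerating all 2 × 2 tables. The treated fraction above the cut is 1 − Φ(c + 1).

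| Controls above cut | Treated above cut | Chi-square power | Loss (points) |
|---|---|---|---|
| 20% | 3% | 26.4% | 51.7 |
| 35% | 8% | 48.6% | 29.6 |
| 50% | 16% | 57.6% | 20.5 |
| 70% | 32% | 60.7% | 17.5 |
| 80% | 44% | 58.9% | 19.2 |

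With a continuity correction, chi-square power at 50% above the cut drops further, to 38%. For a smaller shift of 0.5 SD, the t-test has 28% power against 13% to 20% for chi-square, so neither analysis is strong.

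**3. Power for a skewed score.** SDS was simulated as negative binomial with mean m and variance m + m²/k, 40,000 replicates per row. The Mann-Whitney test on SDS is compared with chi-square on SDS ≥3.

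| Means (control v treated) | k | At or above 3 | Mann-Whitney | Chi-square | Loss (points) |
|---|---|---|---|---|---|
| 3 v 1 | 1 | 42% v 12% | 53.2% | 51.4% | 1.7 |
| 2 v 0.7 | 1 | 30% v 7% | 44.6% | 39.5% | 5.1 |
| 4 v 1.5 | 2 | 59% v 21% | 71.5% | 61.9% | 9.6 |
| 8 v 4 | 1 | 70% v 51% | 31.7% | 20.2% | 11.5 |
| 6 v 3 | 2 | 74% v 48% | 51.3% | 34.4% | 16.9 |
| 8 v 4 | 2 | 82% v 59% | 54.6% | 31.0% | 23.6 |

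(Losses are taken before rounding.) With equal means of 3, both tests reject in about 5% of runs, so the gain is not bought with false positives. The loss is small when the cut happens to separate the arms well, and large when most patients in both arms lie above it.

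**4. Pooled reading.** If both nutrition arms are pooled (32 v 16), the normal approximation gives a loss of about 8 to 32 points for shifts of 0.4 to 1.2 SD and 30% to 80% of controls above the cut.

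These comparisons use a single post-operative score. They do not include the further effect of baseline adjustment, which depends on a correlation the protocol does not give.

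**The case against.** The strongest reply is that the protocol never makes the yes/no defects its perfusion analysis. The three sentences define terms. SSS, SRS and SDS are named numeric quantities, and nothing says they are dropped. The statistical section names no perfusion variable, and its t-test, Mann-Whitney test and linear regression would all fit the scores. The abstract also speaks of changes after CABG, which suits a graded comparison at least as well. Which variable is compared may be settled in the full protocol or the analysis plan, and a condensed article need not cite a source for a reading threshold.

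Most of this stands. A reader might infer that perfusion is reduced to yes/no results, that most of the score is thrown away, or that a particular power loss is usual. The text supports none of these. It leaves the graded analysis open, a single cut keeps about half to two thirds of the information in the normal case above, and no score distribution is given from which a usual loss could follow.

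What survives does not depend on missing detail. The article chose to fix operational perfusion results, and those it gives a meaning to are all dichotomies. Even where its listed tests would reach the scores, an unadjusted two-sample test leaves the baseline scan unused.

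**Conclusion.** The point holds in a limited form: the defined perfusion results are three dichotomies suited to a chi-square test at 16 per arm, and the graded scores are available but not designated. The cost arises only if the yes/no defects carry the comparison. Its size depends on the assumed distributions: about 2 to 24 points of power in the skewed scenarios shown, and about 18 to 52 points for a normal score with a 1 SD shift and 20% to 80% of controls above the cut. The skewed range is the more relevant if SDS piles up near zero after revascularisation. Perfusion is secondary and the study is a proof of concept that makes no power claim, so this is a worthwhile improvement and does not threaten the trial's main conclusions.

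**What to change.** In Outcome measures and Nuclear medicine imaging techniques, name SDS (inducible ischaemia) and SRS (scarring) on their full scale as the perfusion endpoints. In Statistical analysis, state that the post-CABG score is compared between arms with the baseline score as covariate, or by a rank-based equivalent if the scores are skewed. Keep the rates of reversible, fixed and any defect as supportive or descriptive figures. If the full protocol or analysis plan already says this, the article need only be brought into line.

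The cost is a few sentences. The scores are already obtained at both scans, so no new data, reading or procedure is needed. The small drawback is that a score difference is less familiar clinically than a defect rate, which is why the rates stay in the report.

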### Bioelectrical impedance spectrometry

A BIS-measurement (BodyScout, Fresenius Kabi, 's-Hertogenbosch, The Netherlands) is performed at baseline and approximately three weeks after CABG for the assessment of body composition. The principle of the BIS is based on the conductance through body fluid of an electric current (5-800 μA, 5 kHz-1 MHz). The BIS measures the impedance at a range of frequencies from which the resistances of extra-cellular water and intracellular water are extrapolated. Resistance is measured on the right side while patients in supine position. Subsequently, FFM is calculated (FFM is linearly related to height^2^/body resistance) [11].

### Anesthetic and (post-)surgical procedures

Anaesthesia is induced with sufentanil 3 μg kg^-1 ^(Suftena^®^, Janssen-Cilag, Tilburg, The Netherlands) and propofolol 50-100 mg (Fresenius Kabi, Den Bosch, The Netherlands). Pancuronium bromide 0.1 mg kg^-1 ^(Pavulon^®^, Organon, Oss, The Netherlands) is given for muscle relaxation. Morphine 20 mg is given as a slow bolus injection before start of surgery. Anaesthesia is maintained with a continuous infusion of propofolol 2-5 mg kg^-1 ^h^-1^.

The off-pump technique is used for all patients. After a median full sternotomy, a few superficial and deep pericardial sutures are placed to facilitate cardiac displacement. During anastomosis, a suction-type mechanical stabilizer (Octopus 4.3, Medtronic, Minneapolis, MN, USA) is used to immobilize the target site of coronary artery. Distal myocardial perfusion is maintained using intracoronary shunt tube (Anastaflo, Edwards Lifescience, Irvine, CA, USA). The basic strategy for myocardial revascularization is in situ grafting of the internal thoracic artery to the left coronary system with complementary saphenous vein. Vein-to-aorta proximal anastomosis is performed using partial clamping or an anastomotic device.

After surgery, patients are admitted to the ICU and treated according to a standardized clinical protocol. Fluid administration consists of NaCl 0.9% and hydroxyethyl starch 6% of molecular weight 200 kDa (Haes-Steril, Fresenius Kabi, Den Bosch, The Netherlands).

### Blood laboratory analyses

In blood plasma, the concentrations of amino acids, ADMA and SDMA will be analyzed by high performance liquid chromatography (HPLC)/fluorescence as described previously [12,13]. Briefly, solid-phase extraction is used to isolate ADMA, SDMA and arginine, and subsequently all amino acids and ADMA and SDMA are converted into stable adducts by derivatization with ophthalaldehyde reagent containing mercaptopropionic acid. Derivatives are then separated by reversed-phase HPLC using isocratic elution and fluorescence detection.

Blood plasma, concentrations of Troponin T, CK-MB, and NT-proBNP will be analyzed with standard laboratory tests.

PBMC are isolated from whole blood by centrifugation after which cells are washed with PBS, are counted (Cell Dyn 4000, Abbott, Hoofddorp, The Netherlands), and lysed. Finally, the intracellular ADMA concentration in PBMC will be measured by HPLC/fluorescence.

### Tissue laboratory analysis

After homogenization of cardiac or aortic tissue (OMNI 2000 homogenizer, OMNI international Inc., Gainesville, Virginia, USA), concentrations of amino acids, ADMA and SDMA will be analyzed by HPLC/fluorescence. In cardiac tissue, also the activity of DDAH will be determined by measuring citrulline formation during incubation of tissue homogenates with an excess of ADMA. Furthermore, the activity of arginase will be determined by measurement of ornithine formation during incubation of tissue homogenates with an excess of arginine. Both citrulline and ornithine formation will be analyzed by HPLC/fluorescene.

### Tissue pathological evaluation

The cardiac tissue sample will be fixated in formaline. It then will be studied by histological, immuno-histochemical and ultrastructural analysis. For histological analysis, tissue samples will be stained with hematoxylin and eosin (HE) and Elastica van Gieson (EVG). Subsequently, cardiomyocytes diameter, thickness of the endocardium, level of fibrosis (interstitial, replaced and perivascular) and the percentage of fat tissue contribution (replacement and perivascular) will be analyzed. Periodic acid Schiff digested (PAS/D) stained tissue segments will be evaluated to detect and quantify glycogen stacking. Finally, the presence of iron and amyloid will be established by ferron and Congo-red staining respectively. The immuno-histochemical part of the study includes analysis/quantification of lymphocytes, macrophages, neutrophil granulocytes, myocytolysis, and pro-inflammatory vessel damage by antibodies CD45, CD68, myeloperoxidase (MPO), C3d, and carboxymethyl lysine (CML) respectively. Using electron microscopy, we will determine myofibril density, cytosolic glycogen, expanded sarcoplasmatic reticulum (as marker of cellular damage), amount of mitochondria, damage to mitochondria (stacking as reversible damage, protein dots as irreversible damage), and thickness of the basal membrane of capillaries.

All analysis in this study will be done by analysts that are blinded to group assignment.

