#### Parenteral nutrition

Patients in the parenteral group will receive 1250 ml of nutrition (Nutriflex Lipid peri, B.Braun, Oss, The Netherlands) containing amino acids, lipids and glucose. An amount of 1250 ml of the amino acid infusion (840 mOsm/L) will be given in 24 hours for 5 days (Table 3). In addition, vitamins (Cernevit, Baxter, Utrecht, The Netherlands) and trace elements (Nutritrace, B.Braun, Oss, The Netherlands) will be added to the parenteral nutrition. This nutrition will be given two days before, during and two days after CABG. Patients are permitted to eat and drink in addition to their supplemental nutrition.

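### The main outcome of cardiomyocyte structure includes nine chronic tissue features (of 22 readings) that days of feeding are very unlikely to move; light-microscopy glycogen is to be quantified on digested sections

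*Protocol article*

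**What the plan says.** The Outcome measures section of the protocol article states: "The main study outcomes are amino acid profile and cardiomyocytes structure at the time of cardiac surgery". It then says how structure is read: "Cardiomyocytes structure will be assessed by histological analysis, immuno-histochemistry, and by electron microscopy". It names no lead feature and no composite score.

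The Tissue pathological evaluation section gives the content. Besides cardiomyocyte diameter and endocardial thickness, the histology covers "level of fibrosis (interstitial, replaced and perivascular) and the percentage of fat tissue contribution (replacement and perivascular) will be analyzed". It adds that "the presence of iron and amyloid will be established by ferron and Congo-red staining respectively", and on glycogen: "Periodic acid Schiff digested (PAS/D) stained tissue segments will be evaluated to detect and quantify glycogen stacking". Five immunohistochemical and seven electron-microscopic readings follow. One of the latter is the thickness of the capillary basal membrane.

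Under Blood and tissue samples, both right atrial samples are taken during the operation. The baseline visit (Setting, and Table 2) includes blood, impedance and imaging but no cardiac tissue. For the parenteral arm the text says "This nutrition will be given two days before, during and two days after CABG". The enteral arm has the same in-hospital period, preceded by four days of a nutrient drink at home.

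Under Statistical analysis, each active arm is compared with control by unpaired tests at p ≤ 0.05, with regression for confounders that are not named. The Discussion expects nutrition to improve cardiomyocyte structure.

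**The concern.** The outcome puts two kinds of reading side by side. Some could plausibly respond within days, such as glycogen, inflammatory cells and mitochondrial damage. Others record what has accumulated in the tissue over a long time: fibrosis, fat, iron, amyloid, and thickening of the endocardium and capillary basal membrane. The section itself separates reversible from irreversible damage for mitochondria, but nothing similar is done for the outcome as a whole.

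If feeding does not move a chronic feature, a significant difference in it is a false positive. As the outcome is written, that result would count towards the claim that nutrition improves structure. It could not be checked against a pre-treatment value, because none exists, and the planned regression cannot adjust for one.

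The glycogen stain raises a separate problem. Glycogen is the structural reading closest to the article's own rationale, since the Background says that glycogen reserves last only hours in fasting. The light-microscopy method named for it uses sections from which digestion has removed the glycogen.

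**Working it through.** The article gives no effect size, standard deviation or power figure for structure, so there is no plan figure to reproduce.

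**1. Count of readings (Tissue pathological evaluation)**
- Histology: diameter 1, endocardium 1, fibrosis 3, fat 2, glycogen 1, iron 1, amyloid 1 = 10.
- Immunohistochemistry: lymphocytes, macrophages, neutrophils, myocytolysis, vessel damage (CML) = 5.
- Electron microscopy: myofibril density, cytosolic glycogen, sarcoplasmatic reticulum, amount of mitochondria, reversible damage, irreversible damage, basal membrane = 7.
- Total: 10 + 5 + 7 = 22.
- Chronic features: fibrosis 3 + fat 2 + iron 1 + amyloid 1 + endocardium 1 + basal membrane 1 = 9, which is 9/22 = 41%. The remainder is 22 − 9 = 13.

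**2. Feeding before the first tissue sample**
- Parenteral arm: 2 days by the text, 3 by Table 2 (days −3 to −1).
- Enteral arm: 4 + 2 = 6 days by the text, 4 + 3 = 7 by Table 2.
- Range over both arms: 2 to 7 days. The text and Table 2 differ on the in-hospital period and must be reconciled; the argument holds under either.

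**3. What chance alone does to one unaffected feature, 16 v 16**
- Standard error of the difference: √(2/16) = 0.354 SD.
- Difference needed for p ≤ 0.05 (two-sided, assumed; 30 df, t = 2.042): 2.042 × 0.354 = 0.72 SD.
- By construction this happens in 5% of tests.

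**4. Nine unaffected features**
- Independent features, one comparison: 1 − 0.95^9 = 0.370. Expected number of false positives: 9 × 0.05 = 0.45.
- With correlated features, a simulation of 4,000 trials (three arms of 16, shared control, t-tests) gives the chance of at least one p ≤ 0.05:

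| Assumed correlation between features | One arm v control, one sample | Both arms v control, one sample | Both arms v control, both samples |
|---|---|---|---|
| 0 | 37% | 59% | 73% |
| 0.3 | 33% | 53% | 69% |
| 0.6 | 24% | 39% | 60% |

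The last column also assumes a correlation of 0.8 between the two samples of one patient. All nine features are treated as continuous. Iron and amyloid are read as present or absent, so their true test size will differ somewhat from 5%.

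**5. Glycogen**
The section names digested PAS sections for detecting and quantifying glycogen, and the abbreviation list defines PAS/D in the same way. No undigested section is mentioned. The digestion step removes glycogen, so a digested section read alone is the negative control. Glycogen is measured by the loss of stain between an undigested section and its digested neighbour.

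**The case against.** A reader might infer that any difference in these features would be pre-existing imbalance taken for a nutrition effect. The documents do not support that. Allocation is by computer-generated blocks and the analysts are blinded, so imbalance is zero in expectation. A missing baseline costs precision and does not bias the comparison. Sampling and measurement variation also contribute to any observed difference.

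A reader might also take the one-in-three chance of a gap above one standard error (0.35 SD) as the size of the problem. But the plan does not call such a gap an effect; significance needs about 0.72 SD, and the rate is 5% per feature and comparison. Nor do the chronic features dilute the others, since no composite is defined.

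Three further objections carry weight:
- The documents give no rate of change for any feature. That these nine do not move within days is a plausible biological premise, not a stated fact, and the classification is the reviewer's.
- This is a condensed article on a proof-of-concept study. The full protocol or analysis plan may say which readings are tested and which only describe the tissue. Measuring the nine is reasonable in itself. What stands is that the article places them all in a main outcome.
- A paired undigested section may be intended but unreported, and electron microscopy also reads cytosolic glycogen. This limits the harm; the stated light-microscopy method still fails if followed as written.

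**Conclusion.** The concern holds for part of the structural outcome. Nine of its 22 readings are very unlikely to respond to 2 to 7 days of feeding and have no pre-treatment sample. Tested as nutrition effects, they can add little but chance findings. The probability of at least one is about 24% to 37% for one active arm against control on one sample, 39% to 59% with both active arms, and 60% to 73% if both samples are also tested.

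These figures assume that feeding has no effect on the nine, two-sided tests at 0.05 without adjustment, correlations of 0 to 0.6 between features and, for the last range, 0.8 between samples. There is no systematic bias, and the other 13 readings are untouched.

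The glycogen wording is a separate, smaller fault: a stated method that cannot deliver its measurement unless an undigested section is added.

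**What to change.** In Outcome measures and Tissue pathological evaluation:

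- Report the three fibrosis types, the two fat types, iron, amyloid, endocardial thickness and capillary basal-membrane thickness as descriptive tissue characteristics, and draw no conclusion about nutrition from them.
- Keep all 13 other readings in the structural outcome. These include cardiomyocyte diameter, myocytolysis, CML vessel damage, myofibril density, amount of mitochondria and both kinds of mitochondrial damage. None of them was classed as chronic, and the early and late samples could show injury arising during surgery.
- Quantify light-microscopy glycogen as the difference between an undigested PAS section and the adjacent PAS/D section.

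Adjustment for fibrosis is optional at most. Fibrosis is measured after randomisation, so adjustment is safe only if feeding really leaves it unchanged, and any gain depends on correlations that the documents do not give.

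The cost is a change of wording and one routine extra stain on tissue already taken, with no further biopsy. The downside is that fewer features can be claimed as treatment effects. If the nine are not tested as nutrition effects, their contribution to false-positive claims falls to zero.

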### Blood and tissue samples

Blood sampling will be done at baseline (approximately two weeks before CABG during a visit at the hospital outpatient clinic), at the day of surgery (once before and twice during surgery), at the first and third day after surgery, and approximately three weeks after surgery (during a visit at the hospital outpatient clinic) (Table 2).

During surgery, two tissue samples of the appendix of the right atrium will be taken by the surgeon. One sample will be taken prior to the start of the anastomosic connection of the bypass graft, and one sample at the end of the procedure before closing of the pericardium. Half of each sample is placed in an aluminum box which will be immediately frozen in liquid nitrogen and stored at -80°C until the amino acid profile is analyzed. The other half of each sample is immediately placed in formalin and will be analyzed within two weeks for the assessment of cardiomyocytes structure. In addition, a sample of aortic tissue is taken by the surgeon at the end of the CABG-procedure which becomes available due to fixation of the proximal anastomosis needed for the bypass and is in routine clinical practice discarded. The sample is immediately frozen in liquid nitrogen and stored at -80°C until the ADMA concentration is measured.

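### CD45, named as the lymphocyte marker, is carried by all leukocytes, so without a separation step the readout measures total leukocytes and overlaps the CD68 and MPO counts

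*Protocol article*

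**What the plan says.** The section Tissue pathological evaluation describes the immuno-histochemical work as "analysis/quantification of lymphocytes, macrophages, neutrophil granulocytes, myocytolysis, and pro-inflammatory vessel damage by antibodies CD45, CD68, myeloperoxidase (MPO), C3d, and carboxymethyl lysine (CML) respectively". Five targets are matched in order with five antibodies: lymphocytes with CD45, macrophages with CD68, neutrophil granulocytes with MPO, myocytolysis with C3d, and vessel damage with CML. No other lymphocyte marker appears in the article.

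The section Outcome measures gives these readouts their rank. It states that "The main study outcomes are amino acid profile and cardiomyocytes structure at the time of cardiac surgery", and then that "Cardiomyocytes structure will be assessed by histological analysis, immuno-histochemistry, and by electron microscopy". The lymphocyte count is therefore a component of a main outcome, though it is not itself named as an outcome.

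Blood and tissue samples says that two right atrial samples are taken per patient: one before the graft anastomosis and "one sample at the end of the procedure before closing of the pericardium". Under Statistical analysis, the enteral and parenteral groups are compared with control, and "A p-value of ≤ 0.05 will be considered statistically significant".

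**The concern.** CD45 is the leukocyte common antigen. Lymphocytes carry it, and so do monocytes, macrophages and granulocytes. The article does not say this; it is definitional knowledge in pathology and not a finding from a particular study. It follows that the antibody chosen for lymphocytes also labels the two cell types that the plan means to count separately with CD68 and MPO.

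What is at stake is interpretation. The plan evidently intends three distinct cell counts. If the first contains the other two, an effect of nutrition on neutrophils or macrophages alone would also move the count labelled lymphocytes, and one inflammatory signal could be reported as two findings. The Background names impairment of the immune system among the consequences of poor nutrition, so a result labelled as lymphocytes could well be taken as mechanistic evidence. The late biopsy follows surgical manipulation. Some neutrophil entry by then is plausible, but the article gives no cell densities and this is not established.

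**Working it through.** The article states no figure for this readout, so there is none to reproduce. The check is a reading of the marker list followed by simple algebra.

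**Step 1: marker against target**

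| Target in the plan | Antibody in the plan | Cells that carry the marker |
|---|---|---|
| Lymphocytes | CD45 | Lymphocytes, macrophages, neutrophils |
| Macrophages | CD68 | Taken here, as the plan does, to be macrophages |
| Neutrophil granulocytes | MPO | Taken here, as the plan does, to be neutrophils |

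The first two columns come from Tissue pathological evaluation. The CD45 entry in the third column is general knowledge.

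**Step 2: overcount if nothing is separated**

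Let L, M and N be the densities of lymphocytes, macrophages and neutrophils, and let C be the CD45 count. With no separation and equal detection of all three cell types, C = L + M + N. With p = L / C, the lymphocyte share, the overcount factor is C / L = 1 / p. The article gives no value for p, so a range is assumed:

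- p = 0.90: 1 / 0.90 = 1.11
- p = 0.30: 1 / 0.30 = 3.33

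If macrophages and neutrophils are separated out, by morphology or by reference to the CD68 and MPO stains, the factor is near 1.0.

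**Step 3: what passes into an arm comparison**

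If both arms have the same L, and the other cells (M + N) are higher in one arm by a fraction d, the CD45 count is higher in that arm by (1 − p) × d:

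- p = 0.90: 0.10 × d
- p = 0.30: 0.70 × d

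Between 10% and 70% of the relative difference in the other cells would thus show as a lymphocyte difference when the true one is zero. This range rests on the same assumed shares.

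**Step 4: weight among the structure readouts**

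Taking fibrosis, fat and mitochondrial damage as one item each, Tissue pathological evaluation lists 7 histological, 5 immuno-histochemical and 6 ultrastructural items: 7 + 5 + 6 = 18. Counting their subtypes (three of fibrosis, two of fat, two of mitochondrial damage) adds 2 + 1 + 1 = 4, giving 22. The CD45 readout is one of about 20.

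**The case against.** A reader might infer that macrophages and neutrophils are certainly counted a second time as lymphocytes and that the lymphocyte result is therefore wrong. The document does not support that. It would need a rule that every CD45-positive cell is scored as a lymphocyte, and the article states no such rule. The pathologist may separate cells by morphology or by the CD68 and MPO stains planned on the same tissue. Counting rules are also detail that a condensed article commonly leaves to the full protocol or the laboratory procedure. This stands, and the absence of a counting rule is not the point here. The point is that the article does fix the marker, and the one it fixes does not isolate the named cell type.

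A second objection is blinding: "All analysis in this study will be done by analysts that are blinded to group assignment". This removes reader bias and means that any lack of specificity applies to all arms alike. A comparison of CD45-positive cells between arms is therefore valid as a comparison of leukocytes. Blinding does not make the marker specific, however. A blinded reader would faithfully record a neutrophil difference under the lymphocyte label.

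Third, any single worked example is arbitrary. With assumed densities of 10 lymphocytes, 10 macrophages and 5 neutrophils per mm², the CD45 count is 25, or 2.5 times the lymphocytes. A rise in neutrophils to 20 takes it to 40, and 40 / 25 = 1.60, with lymphocytes unchanged. The arithmetic is right, but the densities have no source in the article. The example also describes a change between biopsies, whereas the stated analysis compares groups. It shows the mechanism and nothing about the size in this trial.

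Fourth, the readout is one of many in a study that calls itself proof of concept, and the article defines no composite score into which a double-counted signal would feed. That stands and sets the severity.

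**Conclusion.** The point holds in a limited form. As specified, the readout called lymphocytes rests on a pan-leukocyte marker. Unless an unstated separation step is used, it measures total leukocytes, overlaps with the macrophage and neutrophil counts, and cannot support a conclusion specific to lymphocytes. The size cannot be fixed from the article: about 1.1-fold to 3.3-fold under the assumed lymphocyte shares with no separation, and close to none with separation. Both ends assume equal detection of the three cell types. The issue is minor. It concerns the label and reading of one component of cardiomyocyte structure; the amino acid outcome and the other structure readouts are unaffected.

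**What to change.** Any one of these is enough:

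1. Report the readout as CD45-positive leukocytes and draw no lymphocyte-specific conclusion from it. This works for slides already stained and is compatible with whatever counting rule the full protocol contains. The cost is a less specific label.
2. Keep the lymphocyte label and state that CD68- and MPO-positive cells are excluded. Both stains are already planned on the same samples, so the cost is some extra counting. If exclusion is done by subtracting counts, the result carries the error of three counts and should be described as derived.
3. Use a lymphocyte-specific marker, for example CD3, with CD20 if B cells are wanted. The Setting section says the study is already under way, and Blood and tissue samples has the formalin-fixed halves analyzed within two weeks. A switch midway would leave earlier and later patients measured with different markers. The new marker should therefore be applied to the stored tissue of all patients, provided that it has been kept, which the article does not say for the formalin-fixed halves. The cost is the extra staining.

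The first option is the simplest and costs almost nothing.
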